## Abstract

**Background:**

Worksites are important locations for interventions to promote health. However, occupational programs with documented efficacy often are not used, and those being implemented have not been studied. The research in this report was funded through the American Reinvestment and Recovery Act Challenge Topic 'Pathways for Translational Research,' to define and prioritize determinants that enable and hinder translation of evidenced-based health interventions in well-defined settings.

**Methods:**

The IGNITE (investigation to guide new insights for translational effectiveness) trial is a prospective cohort study of a worksite wellness and injury reduction program from adoption to final outcomes among 12 fire departments. It will employ a mixed methods strategy to define a translational model. We will assess decision to adopt, installation, use, and outcomes (reach, individual outcomes, and economic effects) using onsite measurements, surveys, focus groups, and key informant interviews. Quantitative data will be used to define the model and conduct mediation analysis of each translational phase. Qualitative data will expand on, challenge, and confirm survey findings and allow a more thorough understanding and convergent validity by overcoming biases in qualitative and quantitative methods used alone.

**Discussion:**

Findings will inform worksite wellness in fire departments. The resultant prioritized influences and model of effective translation can be validated and manipulated in these and other settings to more efficiently move science to service.

## Background

Frequently, there is little relationship between the science supporting an intervention and its adoption, and programs are selected based on availability, opportunity or perceived benefits, rather than solid evidence of effectiveness [1]. Most research on moving evidence-based interventions to practice involves programs to alter providers' care patterns or new curricula introduced to schools. Those translational models may differ from worksite dissemination, where adoption is by an organization and participants are asked to alter their existing personal health behaviors, rather than an organization implementing a new curriculum or technology for use with students or clients. No published study has prospectively assessed the complete translation of a worksite health promotion program.

Understanding worksite health promotion is important, as job settings are natural formats for program delivery. Occupational settings have potential to restructure environments and alter social norms, leading to outcomes that benefit both workers and their employers [2,3]. Despite studies documenting reduced healthcare costs and improved employee productivity, evidenced-based worksite interventions often are not used, and those that are used frequently have not been assessed for effectiveness [4,5].

### Conceptual basis and design rationale

This protocol is designed to establish the characteristics of a theory-based, empirically derived framework for worksite translation. Our model's underpinnings are from three perspectives: review of implementation studies [6]; business/organizational psychology [7,8]; and prior experience in the fire departments obtained during the program's development and efficacy trials.

Durlak and DuPre [6] summarized results from more than 500 implementation studies and compared their conclusions and those from two additional reviews. They identified consistent implementation factors related to the setting, the users, the innovation, and its delivery system. Those constructs, along with aspects of an ecological model and organizational analysis, are shown in Figure 1. Final outcomes for our protocol include process evaluation [9], external validity measures of the widely applied RE-AIM framework http://www.re-aim.org, and individual workers' behavioral changes. The framework's sequence of stages provides benchmarks for protocol implementation. In addition, this model will guide the planned mediation analyses.

**Figure 1 F1:**
[figure not shown]
**Framework for Effective Translation**. Modified from Durlak and DuPre [6].

### PHLAME worksite wellness for firefighters

Despite public perceptions about firefighters being fit, their health profile is comparable to other workers, with many prevalent harmful behaviors: unhealthy diet, lack of regular physical activity, and overweight/obesity [10-12]. Firefighters' episodic intense work, combined with those individual health risks, likely contribute to myocardial infarction being the leading cause of on duty death [13]. In addition, perhaps related to exposure to toxins, their risk of cancer is increased [14,15]. The fire service also is one of the most hazardous occupations, and the rate of work-related injuries is four to eight times greater than that of comparable industries [16]. Prior efforts to mandate health promotion within the fire service largely have been unsuccessful [17].

The PHLAME (promoting healthy lifestyles) wellness/injury reduction program was developed, tested for efficacy, and beta-tested with NIH funding. Its effect sizes were moderate for both diet and physical activity behaviors, and injuries were reduced [18-20]. PHLAME is listed on the Cancer Control P.L.A.N.E.T. evidenced-based website for both promoting healthy nutrition and enhancing physical activity http://cancercontrolplanet.cancer.gov/. However, as with other science-based programs, PHLAME has been used by only a few of the more than 30,000 US fire departments housing more than one million firefighters.

PHLAME's theoretical underpinnings are based on the Health Belief Model [21] and Social Cognitive Theory [22], enhanced by peer effects through a cohesive team work structure [23]. The curriculum is a set of 12, 45-minute interactive sessions, which are completed once per week over approximately four months. The sessions are interactive and based on adult learning principles, emphasizing relevance, problem solving, and application of new abilities [24]. Its team-centered, peer-led format is a natural fit for firefighters' work structure. Typically three stable shifts, composed of four to eight firefighters, staff a fire station, with each shift working 24 hours followed by 48 hours off duty. Accordingly, shifts or work groups can become teams, with sessions inserted into their usual activities. Prior to the first session, one shift member is designated as the team leader, and she/he receives orientation with a training DVD and brief instructional manual. To enhance fidelity and ease of use, the program is explicitly scripted with a team leader manual, elective manual, corresponding workbooks, and an expert resource guide. The materials are stored in the station in a team box between sessions to allow access and provide a visual cue concerning the program (Figure 2).

**Figure 2 F2:**
[figure not shown]
**Curriculum components for the PHLAME program**.

Non-comparability among businesses and turbulence within and across sites makes many worksites problematic study environments [25]. The fire service has advantages in their hierarchical structure and relatively stable funding base. However, fire departments differ in components such as their size, location, revenue sources, job descriptions, organizational climate, and competing economic demands. Accordingly, the planned cohort design is anticipated to have sufficient variability in key features to establish a theory-based translational model.

### Aims

The goal is to define a model for successful translation by determining the probability of the specified proximal and distal outcomes with different combinations of influential factors/constructs (*e.g*., dimension of departments, purveyors, change agents, and other contextual factors) among a defined population of 12 varied moderately-sized fire departments in Oregon and Washington. Findings from this project will assist worksites/communities in the adoption and effective use of worksite wellness programs; and the translational model can be validated and manipulated in this and other settings to better understand and make translation more efficient.

## Methods

### Study design and phases

This protocol is a prospective cohort observational study [26,27]. The potential predictors and model constructs are theory-based, clearly defined, and feasible to measure, which will increase generalizability and applicability of findings. Data will be gathered in five phases, with attention to the components of the STROBE Statement [28].

### Phase One: Dissemination for awareness

Information about the PHLAME team program and IGNITE study will be sent to all 70 moderately-sized fire departments (40 to 140 career firefighters) in Oregon and Washington. Three individuals per site will be targeted: fire chief, union president and the 'wellness coordinator,' with a personalized letter, informational brochure, and recruitment DVD. The DVD is a three-minute high-impact video production of PHLAME information, program benefits, and participant testimonials. The International Association of Fire Fighters is a strong union, and contacting the union president is an effort to ensure line firefighter representation in the decision to participate. We anticipate fielding contacts and sharing additional information from departments that express interest. From those expressing interest, we will select departments for PHLAME installation based on their commitment and projected ability to involve more than two-thirds of their career firefighters.

### Phase Two: Decision to adopt

Once interested departments are identified, investigators will select 12 sites, after reviewing demographics and contact notes to identify a spectrum of contextual variables with oversampling of sites in minority and lower socioeconomic status (SES) communities. Information about the decision to adopt will be collected during those sites' initial data gathering visits. To better understand the adoption process, we also will collect data from 24 matched non-adopting departments, using phone interviews of those sent the informational packet. For analysis, we will index the adoption decision as both binary yes/no and as a continuous variable combining confidence and self-efficacy, comparable to self-determination theory decision metrics [29]. These data will be used in our mediation analysis of factors contributing to the decision to adopt a worksite wellness program (Figure 3).

**Figure 3 F3:**
[figure not shown]
**Decisional Balance Mediation Model**.

### Phase Three: Initial site data and program instillation

Once a department is selected, each site will be assessed over three days (one day per shift), thereby accomplishing data collection for all sites over approximately two months. At each visit, we will obtain consents, distribute/collect surveys, acquire limited physiological data -- body mass index (BMI) and blood pressure -- and conduct focus groups and interviews. We anticipate high participation due to our established credibility from our prior research, demonstrated ability to maintain confidentiality, the camaraderie of firefighters, and convenient onsite data acquisition. With our past firefighter research, participation has been approximately 90 percent [18]. Following data gathering, the site visits will allow in-person orientation of most team leaders. In addition, we can establish plans for follow-up visits and ties for technical support during program use.

### Phase Four: Monitoring program use

A program's initial use may be a particularly critical period. As with any new behavior, system inertia must be overcome, and new activities can feel awkward, potentially resulting in early programmatic failures. This period will be an interval of heightened site observations, and we will continue to record and log any assistance required. The translation literature also suggests that change agents/program champions may have key abilities to influence translation within an organization [30]. Accordingly, we will gather data specifically relating to these key members using observations and the post-program surveys.

We also will have random visits (approximately two per site) to observe sessions and conduct focus group data collection of firefighters and department administrators during the latter weeks of program use. While technical support will be readily available when requested, the PHLAME observation efforts will remain separate from the data collection staff.

### Phase Five: Follow-up data and outcomes

Approximately six to eight months following a department's PHLAME installation, we will begin a second round of three-day visits, which will repeat the initial data gathering activities. In addition, the follow-up assessments will include information relating to program outcomes (*e.g*., number participating [reach], dose delivered, dose received by participants, and fidelity to the scripted manual/workbook format). Information will be used in this phase's mediation assessment (Figure 4).

**Figure 4 F4:**
[figure not shown]
**Translation Mediation Model**.

### Data collection instruments

The constructs and components shown in Figure 1 will be assessed in data collection. The questionnaires used will have high face validity, with item selection based on empirical evidence, theory, validity/reliability, and relevance. Many of the constructs will have established relevance and reliability from our prior work [18,20]. We anticipate a nine-page instrument, which in our experience is within the response burden tolerance of firefighters. The individual outcome and demographic measures include anthropometric measures (height, weight, calculated BMI), dietary measures (validated National Cancer Institute [NCI] fruit and vegetable screener [31,32]), self-reported physical activity, sleeping (reliable items modified from Division of Sleep Medicine at Brigham and Women's Hospital worker studies), organizational features [33,34], occupational fatigue items [35], quality of life, and additional individual variables (perceived family impact, age, gender, race/ethnicity, years as a firefighter, current position/job, and years to retirement). Economic outcome data will be of two types: self report injury and illness, and intervention costs, not counting research inputs, as recommended by the Panel on Cost Effectiveness in Health and Medicine [36]. A list of the items making up physical activity, exercise support, nutrition knowledge, diet support and quality of life are available at http://www.public.asu.edu/~[name]/ripl/Phlame.htm.

The focus group and key informant semi-structured interviews will include items that provide additional understanding of model constructs [37]. Open-ended questions to explore emergent themes will be used, with later exploration of relevant domains. The business literature offers findings that will be useful in understanding the antecedents and motivational factors relating to program adoption, including access to resources, proactive personality style, and leadership role efficacy using established, reliable constructs [38]. Information from the human resource literature will be used to assess perceived organizational impact, social consensus/pressure, decision-making style, readiness to change, and climate (clarity of mission and goals, cohesiveness, stress, and openness to change).

### Data analysis

#### Quantitative data

In general this analysis will use SPSS (SPSS, Chicago, IL) and M-Plus for structural equation modeling (SEM). Survey instrument assessment will begin by confirming predicted item constructs, augmented with exploratory factor analysis, to establish reliable summary scales with maximum internal consistency. Having reduced the survey items to a manageable number of robust constructs, the relation of variables in the translational model will be evaluated. For continuous outcomes, structural equation modeling will be used to evaluate relations among variables using model fit indices. For binary or ordinal outcomes, each construct's contribution to predicting group states for outcomes will be conducted using logistic regression analysis. Cross-sectional and longitudinal models will be developed and model fit indices calculated.

Mediation can address how an intervention achieves its effects [39-41], and it will be used to explain relations between the purported mediators and the outcomes as predicted in Figures 3 and 4. The goal of mediation analysis is to determine which aspects of an intervention are contributing to change, and it defines means for their modification and improvement.

#### Qualitative data

Interviews and focus groups will be audiotaped and transcribed. Transcripts will be read for emerging themes, and then imported into atlas.ti software for review and coding into categorical data in the dimensions of interest. Those groupings will begin with our theoretical survey constructs, and those propositions will be refined and expanded as data emerges. The software tabulates frequencies of events or categories, allows chronological assembly to establish patterns and arraying data using different analytic strategies/graphic displays. Findings will be refined with validity checks, including establishing redundancy, respondent validation, and clear exposition of methods.

#### Triangulation of quantitative and qualitative data

The quantitative and qualitative data paradigms will be combined, with adjustment for the particular study phase [42,43]. For the initial decision to adopt, the individual survey items will inform the mediation analysis, and additional decisional aspects explored in the qualitative data. The latter translational sequences will use the combined survey data, with qualitative findings used to expand on, challenge, and confirm survey findings. Combining both analysis types will provide a richer understanding, confirmatory convergent validity, completeness, and confidence of data by overcoming biases in either method used alone.

Gathering qualitative findings also will allow developing case studies [44]. Often in the business community, information is shared as descriptive cases, and for selected departments, we will create case studies, describing the sequence and identified factors relating to translation. Case studies are intense investigations of specific instances, and generally are evaluated for their usefulness and whether the descriptions are contextually complete. We anticipate that these case studies may be useful when sharing findings with the community of firefighters and fire department decision makers.

### Study power

Analysis of cross-sectional survey data for outcomes will have sufficient power to detect small effects, with adjustment of the multilevel structure of the data. For the more comprehensive covariance structure models, power depends on several factors, such as the number of parameters, effect sizes, levels of analysis, and measurement model. Based on rule of thumb ratios of sample size to parameters and Monte Carlo simulation of latent variable models, this study has a power of approximately 0.4 for a small effect, 0.7 for a moderately small effect (halfway between small and medium), and 0.97 for medium effects. In general, the sample size is sufficient to estimate moderately sized latent variable covariance structure models that include constructs at both the individual level and departmental level. We acknowledge that model performance is likely to be overestimated in a single dataset, and internal validation techniques will be used to assess for and correct that possibility [45,46].

Calculating power for the mediation analyses is based on newer techniques that incorporate resampling methods and the distribution of the product. Assuming a small intraclass correlation, we will have 0.8 power to detect moderate effect size mediation relations. Power to detect moderator effects is slightly less and will require at least medium effect sizes for most potential moderators.

Sample size for qualitative data will be based on the criteria of representative and collecting information to saturation, so that additional interview/focus groups do not add to emerging data. However, our intent is to gather data from all participants at each site.

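### The sample is called sufficient for department-level latent constructs, and power is given with no level named, but installation, use and outcomes are observed in only 12 departments

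*Protocol article*

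**What the plan says.** The Study power section makes three statements that bear on this point.

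- On the survey outcomes: "Analysis of cross-sectional survey data for outcomes will have sufficient power to detect small effects, with adjustment of the multilevel structure of the data".
- On the covariance structure models: power of about 0.4 for a small effect, "0.7 for a moderately small effect (halfway between small and medium), and 0.97 for medium effects". The level of these effects is not named, although the preceding sentence lists the level of analysis among the things that drive power.
- On adequacy overall: the "sample size is sufficient to estimate moderately sized latent variable covariance structure models that include constructs at both the individual level and departmental level".

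The number of departments is fixed elsewhere. The Aims section places the work "among a defined population of 12 varied moderately-sized fire departments in Oregon and Washington", and Phase Two says that "investigators will select 12 sites". For the adoption decision only, Phase Two adds: "we also will collect data from 24 matched non-adopting departments, using phone interviews".

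The number of firefighters follows from Phase One, which approaches "all 70 moderately-sized fire departments (40 to 140 career firefighters) in Oregon and Washington", and from Phase Three, where in past firefighter research "participation has been approximately 90 percent".

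**The concern.** The Aims section sets out to relate outcomes to combinations of factors that include features of departments, purveyors, change agents and context. The Conceptual basis and PHLAME background sections count on differences between departments, such as size, revenue and climate, to supply the variability that the model needs. For a factor that takes one value per department, the number of independent observations is the number of departments, and recruiting more firefighters per site does not raise it.

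The adequacy sentence nevertheless puts the departmental level on the same footing as the individual level. Two things are at stake. Between-department paths and fit indices could be reported as part of a prioritised framework when they rest on 12 observations. And a departmental factor that shows no association could be dismissed against a power figure that was never worked out for that level.

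**Working it through.** **Inputs from the protocol.** Departments: 12 for installation, use and outcomes; 12 + 24 = 36 for the adoption decision. Career firefighters per department: 40 to 140, so 12 × 40 = 480 to 12 × 140 = 1,680 in all. At 90% participation that is 432 to 1,512 respondents. Stated power: 0.4 / 0.7 / 0.97.

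**Assumptions (not given in the protocol).** Two-sided alpha 0.05. Small, halfway and medium effects taken as r = 0.1 / 0.2 / 0.3, or as standardised paths of 0.14 / 0.26 / 0.39, or as d = 0.2 / 0.35 / 0.5.

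**Step 1: what the stated powers imply.** They cannot be reproduced directly, because the article does not give the N, alpha, effect sizes, ICC or model behind them. They can be inverted. For a correlation, N = ((1.960 + z(power)) / atanh(r))² + 3:

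- 0.4 at r = 0.1: ((1.960 − 0.253) / 0.1003)² + 3 ≈ 292
- 0.7 at r = 0.2: ((1.960 + 0.524) / 0.2027)² + 3 ≈ 153
- 0.97 at r = 0.3: ((1.960 + 1.881) / 0.3095)² + 3 ≈ 157

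Paths of 0.14 / 0.26 / 0.39 give 150 / 90 / 90, and d = 0.2 / 0.35 / 0.5 gives 291 / 202 / 236 in total. One-sided tests give 195 / 117 / 133, 100 / 69 / 76 and 194 / 154 / 199. Every variant needs roughly 70 to 290 independent units. That is compatible with 432 to 1,512 clustered respondents and a latent measurement model. It is not compatible with 12 or 36 departments.

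**Step 2: size of a department-level model.** With 12 departments the between-department sample covariance matrix has rank at most 12 − 1 = 11. Free covariance parameters in two illustrative models:

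- Two constructs, three indicators each: 4 loadings + 2 factor variances + 1 path + 6 residual variances = 13.
- Three constructs, three indicators each: 6 loadings + 3 factor variances + 3 paths or covariances + 9 residual variances = 21.

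Both exceed the number of departments, and the first is smaller than what would usually be called moderately sized. With 12 or more indicators the between-department matrix is singular.

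**Step 3: power for a correlation between two department-level measures.** Power ≈ Φ(atanh(r)·√(n − 3) − 1.960) + Φ(−atanh(r)·√(n − 3) − 1.960). For n = 12, r = 0.3: 0.3095 × 3 = 0.929, so Φ(−1.031) + Φ(−2.889) = 0.151 + 0.002 = 0.153. The t-test was also simulated:

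| Departments | r | Fisher z | Simulated |
|---|---|---|---|
| 12 | 0.1 | 0.060 | 0.060 |
| 12 | 0.2 | 0.093 | 0.094 |
| 12 | 0.3 | 0.153 | 0.156 |
| 12 | 0.39 | 0.235 | 0.247 |
| 36 | 0.3 | 0.428 | 0.437 |
| 36 | 0.39 | 0.658 | 0.667 |

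A one-sided test at n = 12 gives only 0.24 at r = 0.3 and 0.34 at r = 0.39.

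**Step 4: correlation needed for 0.80 power at n = 12.** By Fisher z, atanh(r) = (1.960 + 0.842) / 3 = 0.934, so r = 0.73. Simulation gives 0.796 at r = 0.71.

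**The case against.** Several points on the other side stand, and they set the limits of the finding.

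- **The 0.97 is not tied to departments.** A reader might infer that the plan claims 0.97 power for department-level effects. It does not. The figure carries no level, and Step 1 shows that it is plausible for individuals. The fault is that the level is left open, next to a sufficiency claim that names both levels.
- **There are 36 departments for one model.** This is true of the adoption decision, but power for a medium effect there is still only about 0.44 to 0.67, and later phases have 12.
- **Some department-level effects could be detected.** A reader might infer that high power is impossible for any departmental factor. For a department-level predictor of an individual outcome with r = 0.3 on the total-variance scale, power is 0.94 to 0.98 at a residual ICC of 0.05 (36 to 126 respondents per site). Such a factor must explain 0.3² = 9% of the total variance, all of it between departments. That sits badly with the small ICC which the plan assumes for its mediation power, but it is not excluded.
- **Many constructs are measured on individuals.** Support for diet and exercise is rated by firefighters, and teams are formed by shift. Associations within departments keep their power.
- **The department-level model is not given.** A reader might infer that it is unidentified or bound to fail. The documents do not support this: two constructs with six indicators have 6 × 7 / 2 = 21 distinct variances and covariances for 13 parameters, so that model is formally identified. The difficulty is unreliable estimates, standard errors and fit from 12 units.
- **Safeguards are planned.** Internal validation, qualitative triangulation and later validation elsewhere all help against over-optimism. None of them adds departments.
- **An article may condense.** The absence of N, ICC and alpha is not in itself the fault. An affirmative claim that 12 departments cannot support is.

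**Conclusion.** The departmental part of the sufficiency claim is wrong as written. Twelve departments cannot reliably support a moderately sized latent model at that level. The powers of 0.4 / 0.7 / 0.97 should be read as individual-level figures, which the text does not say. For correlations between department-level measures, power at a medium effect is about 0.16 (r = 0.3) to 0.25 (0.39) with 12 departments, and 0.80 needs r of about 0.71. For the adoption decision, 36 departments give about 0.44 to 0.67.

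The power figures rest on an assumed two-sided alpha of 0.05 and conventional effect sizes; the parameter counts rest on illustrative models. The rank limit of 11 follows from the number of departments alone. The individual-level analyses are not called into question.

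**What to change.** In the Study power and Data analysis sections:

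1. State power separately for individual-level and department-level effects, each with the N, ICC and alpha used, and give the adoption decision (36 departments) apart from the later phases (12).
2. Limit the 0.4 / 0.7 / 0.97 figures and the latent-model sufficiency claim to individual-level (within-department) constructs, and withdraw the claim for department-level latent constructs.
3. Enter department-level factors as observed scores, report them with intervals that reflect the number of departments, and label them exploratory.
4. Carry out the planned internal validation by leaving out whole departments.

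This does not require departmental factors to be tested one at a time, which would sit poorly with the aim of studying combinations. The cost is rewording, less favourable stated figures and a more modest conclusion about departmental influences. No new data are needed.

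### The single 0.8 power figure for mediation does not hold for the decision-to-adopt model with its yes/no outcome, which rests on 36 departments

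*Protocol article*

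**What the plan says.** The Study power section of the protocol article introduces power for mediation in general terms: "Calculating power for the mediation analyses is based on newer techniques that incorporate resampling methods and the distribution of the product". It then gives one figure: "Assuming a small intraclass correlation, we will have 0.8 power to detect moderate effect size mediation relations". It excepts no mediation model and gives no sample size, alpha, path sizes or ICC value.

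The Data analysis section applies mediation to the relations in Figures 3 and 4. Figure 3 is the decision-to-adopt model. Phase Two says of the adoption data: "These data will be used in our mediation analysis of factors contributing to the decision to adopt a worksite wellness program". The same section fixes the departments. For adopters, "investigators will select 12 sites". For the comparison, "we also will collect data from 24 matched non-adopting departments, using phone interviews of those sent the informational packet". It defines the outcome in two forms: "we will index the adoption decision as both binary yes/no and as a continuous variable combining confidence and self-efficacy".

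Two other places bear on the unit of analysis. Phase One says who receives the information packet: "Three individuals per site will be targeted: fire chief, union president and the 'wellness coordinator". The triangulation section says that individual survey items will feed the adoption mediation. The article does not say whether the department or the respondent is the unit of the adoption model, or how many people will be interviewed in each non-adopting department.

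**The concern.** The 0.8 depends on a small intraclass correlation. That premise suits a model in which many firefighters within a department each supply their own outcome. Adoption coded yes or no is different: a department either adopts or does not, so every respondent in it shares the same value. The information on that outcome is bounded by the number of departments, 12 plus 24, whatever the number of interviews.

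If 0.8 is read as covering this model, a mediator that shows no significant effect will look as though it had a fair test and failed. The study aims to prioritise influences on translation, and the adoption decision is its first stage. With power well below one half, most real moderate mediators of the yes/no decision would be missed, and their ranking would be unstable.

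**Working it through.** **Inputs from the protocol.** 12 adopting departments and 24 non-adopting, so 12 + 24 = 36 (Phase Two). Three people targeted per department (Phase One), so at most 36 × 3 = 108 informants. Departments of 40 to 140 career firefighters, with more than two-thirds to be involved (Phase One); past participation about 90 percent (Phase Three). Stated power 0.8 (Study power).

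**Assumptions, because the protocol gives no values.** Two-sided alpha 0.05; a single mediator with no direct effect; moderate taken as both standardised paths 0.39, or both 0.30; matching ignored.

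**Can the 0.8 be reproduced?** Not from stated inputs, so the question becomes which N would give it. A quick approximation treats the indirect effect as detected when both paths are significant:

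power ≈ Φ(atanh(r)·√(n−3) − 1.96) × Φ(atanh(r)·√(n−4) − 1.96)

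- r = 0.39 (atanh 0.412), n = 71: 0.924 × 0.921 = 0.85. Simulation gives about 0.81 by joint significance and 0.80 to 0.81 by the distribution of the product.
- r = 0.30 (atanh 0.310), n = 112: 0.898 × 0.896 = 0.80. Simulation gives 0.78 at n = 112 and 0.81 at n = 115.

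So 0.8 corresponds to about 70 to 115 independent units.

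**Does the firefighter sample supply that?** Respondents per site lie between 40 × 2/3 ≈ 27 and 140 × 0.9 = 126, so the 12 sites give about 320 to 1,512. Effective N is total/(1 + (m−1)·ICC):

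- 27 per site, ICC 0.05: about 140.
- 126 per site, ICC 0.01: 1,512/2.25 = 672.

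The 0.8 is plausible for the firefighter-level model (Figure 4) if the ICC is small. At ICC 0.10 the effective N is about 90 to 112, enough for paths of 0.39 but just short for 0.30.

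**Adoption model, yes/no outcome.** The outcome is identical within a department, so its within-department correlation is 1. Three informants then give 108/(1 + 2·1) = 36.

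| Check at 36 departments | Power |
|---|---|
| 12 v 24, logistic b-path; a = 0.30 to 0.39, log odds 0.5 to 0.9 per SD | 0.09 to 0.32 |
| 12 v 24, binary outcome cut from a latent variable, paths 0.30 to 0.39 | about 0.13 to 0.33 |
| Same, both paths 0.59 | about 0.71 |
| Plain two-group comparison, 12 v 24, d = 0.5 | 0.29 |
| One continuous value per department, paths 0.30 (joint significance or distribution of the product) | 0.15 to 0.17 |
| Same, paths 0.39 | 0.37 to 0.41 |

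Across these variants, power for moderate paths is about 0.1 to 0.4. The yes/no outcome itself lies in the lower part of that range, up to about one third.

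**Adoption model, continuous index.** This can differ between informants. If all three respond in all 36 departments, effective N is 108/(1 + 2·ICC):

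| ICC | Effective N | Power, paths 0.39 | Power, paths 0.30 |
|---|---|---|---|
| 0.05 | 98 | above 0.9 | 0.64 to 0.78 |
| 0.10 | 90 | about 0.92 | about 0.64 |
| 0.20 | 77 | about 0.86 | about 0.55 |
| 0.50 | 54 | below 0.73 | below 0.40 |

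The first and last rows are bounded by simulated values at neighbouring N (90 and 108; 60).

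**The case against.** The strongest reply is that the adoption model is not simply a 36-unit analysis. The protocol also plans a continuous index of confidence and self-efficacy, which are properties of persons. It says that individual survey items feed this mediation, and it targets three people per department. With three respondents everywhere, a small ICC and paths of 0.39, 0.8 is met. This stands. A reader might infer that 0.8 is impossible for the adoption model in any form, and the documents do not support that.

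The reply has limits. Sending a packet to three people is not a plan to interview three, and the article never gives the number interviewed in non-adopting departments. People in one department judging the same decision may not have a small ICC. At paths of 0.30 the continuous index still falls short. None of this helps the yes/no outcome, which the protocol expressly plans.

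A reader might also infer that low power makes the list of prioritised influences largely chance. That does not follow. At power 0.3 and a false-positive rate of 0.05, false findings outnumber true ones only if fewer than about 0.05/(0.05 + 0.30) = 14 percent of the tested mediators are real, and the protocol gives no such proportion. It also does not say that prioritisation rests on significance tests alone: it uses fit indices, qualitative data on the adoption decision and internal validation.

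Finally, a condensed article need not print every power input. The point here is not a missing input: the article states a figure and extends it to an analysis it names.

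**Conclusion.** The concern holds for the decision-to-adopt mediation model with the yes/no outcome. The stated 0.8 covers all mediation analyses without exception, but this one has 36 independent outcomes, and the small-ICC condition cannot apply to it. Power for moderate paths is about 0.1 to 0.4, and even paths of 0.59 give only about 0.71.

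These figures rest on an assumed alpha of 0.05, assumed paths of 0.30 to 0.39 and a single mediator, with matching ignored. No single value within the range can be read from the protocol. That 0.8 is out of reach at moderate paths does not depend on which value in that range is taken.

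For the continuous index, 0.8 is conditional on respondent numbers the protocol does not fix. For the firefighter-level model, 0.8 is plausible if the ICC is small. The fault is therefore one of scope: a figure that can be right for one model is stated for all.

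**What to change.** - Limit the 0.8 statement to firefighter-level mediation (Figure 4).
- For the adoption model, state the unit of analysis and the planned number of informants per department, for adopters and non-adopters alike.
- Give that model its own power: about 0.1 to 0.4 for moderate paths with the yes/no outcome, and a separate figure for the continuous index, conditional on respondents per department, ICC and path size. State the alpha and path sizes used.
- Report its mediation estimates with confidence intervals as exploratory, so that a null result is not read as evidence against a mediator.

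The cost is a less favourable stated power for this phase. The change is to wording and reporting; no added data collection is needed.
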